### Primary and secondary outcomes

The primary outcome is the diagnostic of ILD, both IPF and NSIP, versus control subjects or COPD. We will assess the predictive performance of the *DeepBreath* algorithm-evaluated lung auscultation and LUS in the following identification and risk stratification tasks as follows: (1) to discriminate ILD from control subjects (according to expert clinical diagnosis [42]); (2) to differentiate ILD from COPD; (3) to predict ILD clinical severity (according to a HRCT grading scale^1^ and lung function tests^2^); and (4) to differentiate the subcategories of ILD (such as IPF, NSIP) according to the gold standard diagnosis [2, 43, 44]).

Secondary outcomes are the clinical, functional and radiological characteristics of IPF, NSIP and COPD diagnosis. We will: (1) compare the predictive performance of human, expert-identified acoustic and LUS signatures in the above predictive tasks (Kappa coefficient); (2) assess diagnostic performance of a model trained to detect crackles; (3) explore the utility of adding clinical data (signs, symptoms, demographics, medical history and basic paraclinical tests) to the breath sound algorithms; and (4) determine the impact of the diseases on subjects’ health-related quality of life measured with the standardised King’s Brief Interstitial Lung Disease (K-BILD) [47], the COPD assessment test (CAT) [48], and the 36-item Medical Outcomes Study Short-Form Health Survey (SF-36) [49] severity assessment questionnaires.

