## AI algorithms

### Diagnostic and risk stratification algorithms

We will develop *DeepBreath*, a deep learning algorithm to detect the acoustic signatures of IPF, NSIP and COPD from lung sounds. While several state-of-the-art approaches will be tested, the general framework is summarised in Fig. 2. Digital lung auscultations will first be cleaned to crop non-biological frequencies and amplitudes generated by ambient noise not filtered by the stethoscope’s active noise cancelling. The sounds will then be divided into overlapping time windows of between 1 and 10 s and transformed to Mel Frequency Cepstral Coefficients (MFCCs). Several data augmentation techniques will be explored, such as amplitude scaling, pitch shift and random time shift. The effect of each pre-processing method will be tested and the best performing approach according to sensitivity and specificity will be reported. This dataset will then be fed into various deep learning networks (such as convolutional neural networks, Long Short-Term Memory models [LSTM], Transformer architectures, etc.). A prediction on each segment will then be aggregated to represent a patient (including all anatomic sites) and binary classification into positive *vs* negative for diagnostic results will be performed for ILD or control subjects, ILD or COPD, and (if ILD-positive) IPF or NSIP. The same prediction will also be made using LUS images. Risk stratification will use multiclass or regression according to scales obtained from clinical interpretation of LUS, lung function tests, HRCT imagery, K-BILD or CAT, and SF-36 quality of life questionnaires.

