### Sample size calculation

Each patient will provide 10 audio recordings of 30 s. Samples will be considered at the patient level with all 10 recordings. In deep learning, sample size calculation is an intractable problem that is usually discovered through empirical investigation. The number of samples required to reach a certain performance criterion is dependent on the characteristics of the dataset, the diversity and number of the classes, the degree of data augmentation possible, as well as the complexity of the learning algorithm. Thus, sample size calculations cannot rely on the traditional statistical heuristics that are often used in biostatistics. Rather, sample size estimations in deep learning are mostly made by analogy. Evaluating existing knowledge on similar datasets, we find that the expected proportion of velcro-like crackles in IIP patients is nearly 100% [4], whereas the prevalence of coarse crackles is 71% in COPD patients [58]. The exclusivity of these sounds among groups is not known, but overlap is assumed to be minimal and pathological sounds are by definition absent in non-ILD and non-COPD control subjects. Assuming a similar discriminative power compared to a previous work done by our group (personal communication) to distinguish between normal and pathological lung sounds in pneumonia from 80 patients in balanced classes (40 pathological; 40 controls) with 8 auscultation sites of 30 secs each, we estimate using the same number of patients in each class to achieve convergence at above 80% of the area under the receiver operating characteristic curve (AUROC). Thus, we will aim to enrol at least as many patients in each group: 80 ILD (40 IPF, 40 NSIP); 40 COPD; and 40 controls (i.e., known not to have ILD or COPD, and with normal lung function). As the recruitment site would expect 120 ILD patients (40% with IPF; 60% with NSIP) and 100 with COPD over the space of one year, this number is achievable in the time frame of the study (6 months), even with a 70% consent rate.

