### Statistical analysis plan

For descriptive statistics related to the clinical data collected, all continuous variables will be reported as medians with their interquartile ranges. Binary and categorical variables distribution will be reported as proportions and percentages. To evaluate baseline demographic differences and outcomes differences between the case and control patients, conditional logistic regressions will be used to account for the matched design. Pearson’s and Spearman’s correlation coefficients will be used to assess the relationship between continuous variables normally and non-normally distributed, respectively. For the primary outcome, each task will be quantified using descriptive statistics (i.e., proportion and type of abnormalities), as well as the AUROC, sensitivity, specificity, positive predictive value, negative predictive value, and likelihood ratios (with 95% CIs over a fivefold cross-validation).

The diagnostic accuracy of each echographic sign will be assessed and sensitivity, specificity, positive predictive value, negative predictive value, positive likelihood ratio, and negative likelihood ratio with their 95% CIs will be calculated. To find the combination of echographic signs with the best diagnostic accuracy, we will compare the performance of several multivariable models, such as logistic regression, random forest and neural networks. Performance will be reported on a test set comprising 20% of the data in a tenfold cross-validation with 95% CIs. As a secondary objective, we will aim to compare the predictive performance of human expert-identified acoustic signatures in the above predictive tasks. First, we will describe the expert labels by the percentage of sound labels attributed to each diagnosis. A multivariable logistic regression will be derived using the clinical data and sound labels to estimate the diagnoses, as for the primary objective. A kappa score will be used to assess the concordance between *DeepBreath* and expert diagnosis consolidated into a basic predictive model.

The K-BILD, CAT and SF-36 questionnaires will be analysed with descriptive statistics. Associations between the questionnaires’ sum scores and lung function parameters will be quantified by Spearman’s rank correlation coefficient. We will consider correlations < 0.3 as negligible, ≥ 0.3 to < 0.5 as low, ≥ 0.5 to 0.7 as moderate, and ≥ 0.7 as strong.

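### ILD severity is modelled as a graded or continuous outcome, but the analysis section scores every primary task with two-class accuracy measures that fit it poorly

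*Protocol article*

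**What the plan says.** All references are to the protocol article.

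- **Primary and secondary outcomes.** Four tasks stand under the primary outcome. The third is "to predict ILD clinical severity", referenced to an HRCT grading scale and to lung function tests. Each reference carries a footnote marker.
- **Diagnostic and risk stratification algorithms.** Binary classification is assigned to three comparisons: "diagnostic results will be performed for ILD or control subjects, ILD or COPD, and (if ILD-positive) IPF or NSIP". Severity is not among them. It is handled separately: "Risk stratification will use multiclass or regression according to scales obtained from clinical interpretation of LUS", followed by lung function, HRCT and the questionnaires.
- **Statistical analysis plan.** One rule covers all four tasks: "For the primary outcome, each task will be quantified using descriptive statistics (i.e., proportion and type of abnormalities), as well as the AUROC, sensitivity, specificity". The list continues with "positive predictive value, negative predictive value, and likelihood ratios (with 95% CIs over a fivefold cross-validation".
- The same section has a general provision just before that rule: "Pearson’s and Spearman’s correlation coefficients will be used to assess the relationship between continuous variables normally and non-normally distributed, respectively". It is not linked to task 3.
- **Sample size calculation.** Recruitment is "80 ILD (40 IPF, 40 NSIP); 40 COPD; and 40 controls", so 80 patients contribute to the severity task.

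**The concern.** The modelling section and the analysis section do not fit together for task 3. The first produces a grade or a number. The second asks for measures built on a two-way split of the truth. Whoever runs the analysis must fill the gap, either by cutting the severity scale or by scoring each grade against all others.

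A cut discards information from the only 80 patients who contribute, and if it is not fixed in advance it can be chosen after the data are seen. Grade-against-rest scoring treats an error of one grade like an error of three. Neither measures how far predicted severity lies from observed severity.

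This matters for the study's own argument. The Discussion gives the near-absence of severity classification in earlier work as one of the main reasons for doing this study.

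**Working it through.** **1. Do the measures fit the tasks?**

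| Primary task | Model output (algorithms section) | Measures stated (analysis section) | Fit |
|---|---|---|---|
| 1. ILD v control | binary | AUROC and two-class measures | yes |
| 2. ILD v COPD | binary | same | yes |
| 3. ILD severity | multiclass or regression | same | regression: only after a cut; multiclass: one against the rest, order ignored |
| 4. IPF v NSIP | binary | same | yes |

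No measure elsewhere in the section is assigned to task 3. The kappa is for agreement between the algorithm and expert diagnosis. The Spearman analysis with strength bands is for questionnaire scores against lung function. The Pearson/Spearman sentence is general.

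**2. Inputs for the size of the effect**

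- From the document: 40 IPF + 40 NSIP = 80 ILD patients; two-sided 5% tests; fivefold cross-validation.
- Assumed, because the document gives no figure: a normal severity score; a split between 50/50 and 10/90; a true correlation r between predicted and observed severity of 0.3 to 0.5.
- The plan states no precision or power figure for task 3, so there is none to reproduce.

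**3. Information kept after one cut**

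For a normal score cut at quantile p, the fraction kept is φ(z_p)² / [p(1 − p)].

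- Median: 0.3989² / 0.25 = 0.637; 80 × 0.637 = 51 patients.
- 25/75: 0.3178² / 0.1875 = 0.539; 80 × 0.539 = 43 patients.
- 10/90: 0.1755² / 0.09 = 0.342; 80 × 0.342 = 27 patients.

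**4. Information kept with ordered grades**

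For k equal classes analysed as ordered, the fraction kept is k × Σ(φ_i − φ_{i+1})², where φ_i is the normal density at the i-th class boundary (zero at both ends).

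- k = 3: 0.793 (63 patients)
- k = 4: 0.861 (69 patients)
- k = 5: 0.897 (72 patients)

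Grades therefore lose far less than one cut, provided their order is used.

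**5. Power to show any association, n = 80**

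Power ≈ Φ(atanh(r′)·√77 − 1.96), with r′ = r on the full scale and r′ = r·√(fraction kept) after a cut. Example at r = 0.3: full scale, 0.3095 × 8.775 = 2.716, power 0.775; median split, r′ = 0.239, 0.2441 × 8.775 = 2.142, power 0.572.

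| True r | Full scale | Median split | 25/75 split |
|---|---|---|---|
| 0.3 | 0.78 | 0.57 | 0.50 |
| 0.4 | 0.96 | 0.83 | 0.76 |
| 0.5 | 1.00 | 0.96 | 0.92 |

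Simulation with 20,000 runs, done at r = 0.3 and 0.4, agrees to within about 0.02 (at r = 0.3: 0.78, 0.58, 0.50). Rank-based tests (Spearman on the full scale, Mann-Whitney after the cut) give 73%, 55% and 48% at r = 0.3, and 99.6%, 95% and 92% at r = 0.5.

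**6. Precision within a fold**

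80 / 5 = 16 ILD patients per test fold, or 8 against 8 after a median split. The Hanley-McNeil standard error of an AUROC of 0.80 is then about 0.11.

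**The case against.** A reader might infer that task 3 cannot be scored at all as written, or that severity must be dichotomised. The document does not support either.

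- **Multiclass is one of the two allowed models.** Sensitivity, specificity and predictive values can be reported grade by grade, and AUROC has multiclass forms. This objection stands. What remains is that no such rule is stated, that it ignores grade order, and that it does nothing for the regression option.
- **The severity scales carry two footnotes that are not in the text shown.** They may define grades or cuts, so it cannot be said that the plan lacks them. Even so, several grades would still not fit two-class measures directly, and a single binary cut would conflict with multiclass or regression modelling.
- **Correlation is already provided for.** The general Pearson/Spearman sentence could be stretched to predicted against observed severity. It is not assigned to this task, and correlation alone does not show prediction error or calibration.
- **The power figures rest on weak correlations and on a test that the plan does not state.** This also stands. Under the same normal model, r = 0.3 corresponds to an AUROC of about 0.64 at a median split, and an AUROC of 0.80, the study's only stated target, needs r of about 0.64. Where the algorithm does that well, a cut costs almost no power.
- **A journal article may leave metric detail to a fuller document.** True of omitted detail. Here, however, the article states a rule for every task, and that rule does not suit one of them.

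**Conclusion.** The mismatch is real and lies within the article: the measures stated for every primary task do not suit the way severity is modelled. For a regression output the threshold measures do not exist without a cut. For grades they work only one against the rest and lose the ordering.

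The cost depends on what is done. One cut of a normal score keeps at most about 64% of the information; ordered grades analysed as such keep about 79% to 90%. The loss of power is material if the true correlation is about 0.3 to 0.4 and small at 0.5 or above. Score distribution, cut and correlation are all assumptions.

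It would go too far to say that task 3 has no valid result, or that no cut is defined anywhere: the multiclass route exists and the footnotes are not visible. Severity is moderate. The three diagnostic tasks are correctly scored, and the sample size needs no change on this account.

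**What to change.** In the Statistical analysis plan section:

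- Limit AUROC, sensitivity, specificity, predictive values and likelihood ratios to ILD v control, ILD v COPD and IPF v NSIP.
- For severity, report out-of-fold performance on the full scale. Suitable choices are mean absolute error, rank correlation and calibration for lung function, and weighted kappa or an ordinal c-index for the HRCT grade.
- Give each with a 95% confidence interval computed at patient level, for example by bootstrap.
- Treat any AUROC at a pre-specified severity cut, or any grade-against-rest result, as supportive.

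The cost is a few sentences and a few lines of code. No further patients or data are needed.

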## Methods

### Study design

This is a single-centre, prospective, population-based, case–control study that will be carried out in subjects with IPF, NSIP and COPD within a pulmonology outpatient clinic in Switzerland, with a total of approximately 7000 specialised consultations per year. Figure 1 shows the study flowchart and Table 1 details the study schedule. The present study protocol adheres to the Strengthening the Reporting of Observational studies in Epidemiology (STROBE) Statement [41].

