### Population

Inclusion criteria are consecutive, consenting adult outpatients (> 18 years) with IPF (group 1), NSIP (group 2) and COPD (group 3) already diagnosed prior to the consultation (index) date. Probable and definitive IPF diagnosis will be made according to the Fleischner Society Consensus [42], NSIP diagnosis with the American Thoracic Society classification [2, 43], and COPD with the Global Initiative for Chronic Obstructive Lung Disease criteria [44]. Consenting, age-matched (± 2.5 years) individuals with normal lung function (spirometry, lung volume and transfer factor for carbon monoxide [TL_CO_]) followed in the outpatient clinic with a similar quality of electronic medical records, but for diseases other than the outcome of interest, will serve as the 1:1 control group (group 4). This latter group will comprise patients with obstructive sleep apnoea, follow-up of occupational lung diseases (miners, chemical workers, etc.), and follow-up of pulmonary nodules (considered benign after 2 years). Reasons for pulmonary follow-up among the controls will be reviewed and reported in a supplementary file. Identifying all cases with the outcome of interest and selecting controls for comparison is a more efficient and resource-sparing study design than a full cohort study. Exclusion criteria are: (1) patients who cannot be mobilised for posterior auscultation; (2) those known for severe cardiovascular disease with pulmonary repercussions; (3) patients known for a concurrent, acute, infectious pulmonary disease (e.g., pneumonia, bronchitis); (4) patients known for asthma exclusive from COPD; (5) patients with alpha-1-antitrypsin deficit; (6) a physical inability to follow procedures; and 7) inability to give informed consent.

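### PPV and NPV are planned from a case-control sample with fixed group sizes and no stated prevalence, so as written they would reflect the recruitment quota

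*Protocol article*

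**What the plan says.** All references are to the protocol article.

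- **Design.** Study design: "This is a single-centre, prospective, population-based, case–control study". Under Population, the cases are patients "already diagnosed prior to the consultation (index) date", and controls are clinic patients with normal lung function who are followed for other conditions.
- **Group sizes.** Sample size calculation sets "80 ILD (40 IPF, 40 NSIP); 40 COPD; and 40 controls". The same section gives the site's expected yearly numbers: 120 ILD patients, of whom 40% have IPF and 60% NSIP, and 100 COPD patients.
- **Tasks.** Primary and secondary outcomes: "The primary outcome is the diagnostic of ILD, both IPF and NSIP, versus control subjects or COPD". The algorithm section describes pairwise binary classifications: "ILD or control subjects, ILD or COPD, and (if ILD-positive) IPF or NSIP".
- **Metrics.** For the primary outcome, the Statistical analysis plan lists AUROC, sensitivity, specificity, "positive predictive value, negative predictive value, and likelihood ratios (with 95% CIs over a fivefold cross-validation"). It repeats the predictive values for ultrasound: "The diagnostic accuracy of each echographic sign will be assessed and sensitivity, specificity, positive predictive value, negative predictive value".
- **Prevalence.** The article gives no prevalence, reweighting or conversion for PPV or NPV. The limitations in the Discussion do not mention that predictive values depend on the sampling ratio.

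**The concern.** PPV and NPV depend on how common the target condition is among those tested. In a cohort of people presenting for diagnosis, the sample supplies that frequency. Here the investigators supply it by choosing how many patients to enrol per group. A predictive value computed from the sample counts then describes the chosen ratio, and its confidence interval covers sampling error only, not the gap between the quota and any real case mix.

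Consecutive recruitment does not repair this. The quotas depart from the site's own expected mix in both comparisons where the article gives one, and the control group has no natural frequency at all.

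The risk lies in how the results are read. Background and Discussion point to primary care patients with non-specific chronic respiratory symptoms, and the design is labelled population-based. A PPV near 0.9 printed beside the primary result could be taken as the chance that a positive patient in that setting has ILD. The sample NPV would err in the other direction and understate rule-out value where ILD is less frequent than in the sample.

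**Working it through.** **Stated figure.** 80 + 40 + 40 = 160, which agrees with the Abstract's 120 patients plus 40 controls. The article states no PPV, NPV or prevalence, so there is no predictive value to reproduce.

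**Share of positives fixed by the quota, against the site's expectation.**

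| Task | Quota share | Site share |
|---|---|---|
| ILD v control | 80/120 = 66.7% | none given |
| ILD v COPD | 80/120 = 66.7% | 120/220 = 54.5% |
| IPF v NSIP | 40/80 = 50% | 40% |

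**Formulas**, with Se = sensitivity, Sp = specificity and p = share of positives:

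- PPV = Se·p / [Se·p + (1 − Sp)(1 − p)]
- NPV = Sp(1 − p) / [Sp(1 − p) + (1 − Se)p]
- LR+ = Se/(1 − Sp) and LR− = (1 − Se)/Sp, neither of which contains p

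**Main case, Se = Sp = 0.80.** This is an assumption; the article gives only an AUROC target above 80%.

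- Quota, 80 ILD v 40 others: 64 true positives, 16 false negatives, 32 true negatives, 8 false positives. PPV = 64/72 = 0.889; NPV = 32/48 = 0.667.
- Site mix, 120 ILD v 100 COPD: 96, 24, 80 and 20. PPV = 96/116 = 0.828; NPV = 80/104 = 0.769.
- Assumed p = 10%: PPV = 0.08/(0.08 + 0.18) = 0.308; NPV = 0.72/(0.72 + 0.02) = 0.973.
- IPF v NSIP: PPV/NPV = 0.800/0.800 at the 50% quota and 0.727/0.857 at the site's 40%.
- LR+ = 0.80/0.20 = 4.0 and LR− = 0.20/0.80 = 0.25 in every case.

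**Sensitivity to the assumed accuracy** (PPV/NPV). The value 0.724 is what AUROC 0.80 implies at a symmetric threshold under an equal-variance binormal model.

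| Se = Sp | Quota 66.7% | Site ILD:COPD 54.5% | Assumed 10% |
|---|---|---|---|
| 0.70 | 0.824/0.538 | 0.737/0.660 | 0.206/0.955 |
| 0.724 | 0.840/0.568 | 0.759/0.686 | 0.226/0.959 |
| 0.80 | 0.889/0.667 | 0.828/0.769 | 0.308/0.973 |
| 0.90 | 0.947/0.818 | 0.915/0.882 | 0.500/0.988 |

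At Se = Sp = 0.80, other assumed prevalences give 0.500/0.941 at 20%, 0.174/0.987 at 5% and 0.039/0.997 at 1%.

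**Two checks that the ratio drives the result.**

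- A test with no information (Se = Sp = 0.5) gives PPV 0.667 and NPV 0.333 at the 2:1 quota.
- Population says the controls "will serve as the 1:1 control group (group 4"), while Sample size calculation gives 80 ILD to 40 controls. With Se = Sp = 0.80, PPV for ILD v control is 0.80 at 1:1 and 0.89 at 2:1, with no change in the algorithm.

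**The case against.** The strongest reply is that nothing in the plan turns on PPV or NPV. The only performance target is the AUROC, pre-processing is chosen on sensitivity and specificity, and the likelihood ratios already planned let a reader convert to any prevalence. The Discussion adds that the output will not guide diagnosis or treatment, that dedicated validation is needed, that selection bias is possible and that this is a pilot. All of this stands and limits the weight of the point. It does not make the listed predictive values meaningful, because none of those caveats mentions the sampling ratio.

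A second reply is that the article names the metrics without saying how they will be calculated, and that a fuller plan could set a reference prevalence. That is fair: computation from the sample counts is the plain reading, not an explicit statement.

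A third is that most of the dramatic contrast comes from assumed low prevalences. This is also right. The only case mix in the article for ILD v COPD moves PPV from 0.89 to 0.83 and NPV from 0.67 to 0.77.

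A fourth is that converted values inherit their own error. Sensitivity and specificity from established specialist-clinic cases set against controls with normal lung function may not carry over to undifferentiated patients. This stands, and the fix must say so.

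**Conclusion.** The point holds, at moderate weight. Followed as written, PPV and NPV for the binary tasks and the ultrasound signs would reflect the enrolment quota, and their confidence intervals would not show it. With Se = Sp = 0.80, the departure is 0.89/0.67 at the quota against 0.83/0.77 at the site's ILD:COPD mix. In a setting with an assumed 10% prevalence the values would be 0.31/0.97. The accuracy values and every prevalence other than the site's 55% and 40% are assumptions.

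Three stronger readings are tempting but are not supported:

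- **That the primary analysis is invalid.** AUROC, sensitivity, specificity and likelihood ratios do not depend on the sampling ratio, so the primary outcome can still be reported.
- **That a realistic prevalence follows from 120 ILD patients and about 7000 consultations a year.** Consultations are visits, not patients, so 120/7000 is not a prevalence.
- **That a 2:1 quota distorts every task.** IPF v NSIP is 1:1. The mechanism is the same there, but the shift is from 50% to 40%. Severity is modelled as multiclass or regression, so PPV is not defined for it without a cut-off.

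**What to change.** In the Statistical analysis plan section:

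1. Drop sample-based PPV and NPV for the binary tasks and the ultrasound signs. Keep AUROC (for the tasks), sensitivity, specificity and likelihood ratios with their confidence intervals, as already planned.
2. If predictive values are wanted, derive them by Bayes' rule at stated prevalences: 55% for ILD v COPD and 40% for IPF v NSIP (the site mix), and a stated, openly assumed low-prevalence range for ILD v control only. A low range has no evident meaning for the other two tasks, which condition on having one of two diseases.
3. Carry the intervals through from sensitivity and specificity. At a fixed p, the odds of PPV equal LR+ × p/(1 − p) and the odds of (1 − NPV) equal LR− × p/(1 − p), so the limits for the likelihood ratios convert directly.
4. Add a caveat that sensitivity and specificity from established specialist-clinic cases may not transfer to primary care, and that the converted intervals do not cover this.
5. Reconcile the 1:1 control wording under Population with the 80 to 40 allocation under Sample size calculation.

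The cost is a few sentences and a small table. No further data or patients are needed. The drawback for the investigators is that the reported PPVs will look less favourable.

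### The ultrasound-sign analysis pairs a 20% test set with tenfold cross-validation, and primary intervals built from the spread of five folds would fall short of 95% coverage

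*Protocol article*

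**What the plan says.** The section Statistical analysis plan of the protocol article describes two validation schemes.

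- **Primary outcome tasks.** AUROC, sensitivity, specificity, predictive values and likelihood ratios are to be given "with 95% CIs over a fivefold cross-validation". The section Diagnostic and risk stratification algorithms lists the binary tasks as ILD or control, ILD or COPD, and IPF or NSIP within ILD. It adds, for ultrasound: "The same prediction will also be made using LUS images".
- **Models of ultrasound signs.** The aim is stated as "To find the combination of echographic signs with the best diagnostic accuracy, we will compare the performance of several multivariable models", and then: "Performance will be reported on a test set comprising 20% of the data in a tenfold cross-validation with 95% CIs".

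The section Sample size calculation fixes the groups at "80 ILD (40 IPF, 40 NSIP); 40 COPD; and 40 controls", 160 patients in all, and the unit of analysis: "Samples will be considered at the patient level with all 10 recordings". The article gives no formula for either interval. It mentions neither repeated splits nor a hold-out set with tuning inside the remainder.

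**The concern.** There are two separate problems.

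1. The number of folds fixes the test share in plain cross-validation, so 20% and tenfold cannot both describe one such scheme. Two analysts working in good faith could carry out different analyses. If the choice is left until results exist, it can also follow the results.

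2. An interval taken over the folds most naturally means the mean of five fold results plus or minus a multiple of their standard error. The five results are not independent, because any two training sets share most of their patients, and five values give only four degrees of freedom for the variance. Such an interval promises more certainty than it delivers. Here it would sit on the primary outcome, whose stated expectation is "above 80% of the area under the receiver operating characteristic curve (AUROC".

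A smaller consequence is that ultrasound deep learning and the ultrasound-sign models would be trained on different shares of the data and scored on different splits, which makes a comparison between them less clean.

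**Working it through.** **Inputs.** From the article: 80 ILD (40 + 40), 40 COPD and 40 controls; a 20% test share with tenfold; fivefold for the primary tasks; an expected AUROC above 0.80. Assumed, because the article does not give them: the interval formula, the learner and the number of features.

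**Step 1. Test share.** Plain k-fold tests 1/k of the patients per fold.

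- Tenfold: 160/10 = 16 patients, 10%.
- Fivefold: 160/5 = 32 patients, 20%.

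The stated 20% does not reproduce under tenfold.

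**Step 2. Readings that keep both numbers.** There are two: ten repeated random 80/20 splits, or a fixed 20% hold-out with tenfold tuning in the other 80%. The Hanley–McNeil standard error of an AUROC A, with n₁ and n₀ patients, shows what a hold-out costs:

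SE² = [A(1−A) + (n₁−1)(q₁−A²) + (n₀−1)(q₂−A²)] / (n₁n₀), where q₁ = A/(2−A) and q₂ = 2A²/(1+A).

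At A = 0.80, q₁ − A² = 0.0267 and q₂ − A² = 0.0711. For 80 v 40, SE² = (0.16 + 79 × 0.0267 + 39 × 0.0711)/3200 = 0.00158, so SE = 0.040 and 1.96 × SE = 0.078. In the same way:

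| Patients scored | Half-width |
|---|---|
| 80 v 40, each once | ±0.08 |
| 40 v 40, each once | ±0.10 |
| 16 v 8, one 20% hold-out | ±0.18 |
| 8 v 8, one 20% hold-out | ±0.23 |

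The hold-out interval is more than twice as wide. These figures treat the classifier as fixed and ignore training variability.

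**Step 3. Intervals from the spread of folds.** Coverage of mean ± quantile × SD/√J was simulated twice, with different learners: ridge logistic regression (10 features, true AUROC about 0.77, 800–1000 data sets per setting) and a linear discriminant (8 or 20 features, AUROC about 0.8, 1500 data sets per setting). Group sizes were 80 v 40 and 40 v 40.

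| Nominal 95% interval | Ridge | Discriminant |
|---|---|---|
| Five folds, t quantile | 88–91% | 89–93% |
| Five folds, 1.96 | 78–81% | 77–85% |
| Ten 80/20 splits, t quantile | 70–73% | 70–73% |

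Part of the shortfall with 1.96 comes from the quantile alone. With four degrees of freedom, 1.96 covers 87.8% even if folds were independent, which is 7.2 points of a total shortfall of 10 to 18 points (95 − 85 and 95 − 77).

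**Step 4. Correction for overlap.** The corrected variance is s² × (1/J + n_test/n_train), with a t quantile on J − 1 degrees of freedom.

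- Fivefold: 1/5 + 1/4 = 0.45 against 1/5 = 0.20 uncorrected. The interval widens by √(0.45/0.20) = 1.5. Simulated coverage is 97% (ridge).
- Ten 80/20 splits: √((0.10 + 0.25)/0.10) = 1.87. Simulated coverage is 91–92% (discriminant) and 92% (ridge).
- A patient-level bootstrap of pooled out-of-fold predictions covered 89–90% (ridge).

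**The case against.** The strongest reply is that the article never says how the intervals are calculated. An article commonly leaves that formula to a fuller plan, which is not shown here. The phrase for the primary outcome could also describe one interval from pooled out-of-fold predictions, and the sentence on the sign models says only that intervals will be given. This stands, so the coverage finding is conditional on fold spread being the basis. It does not remove the conflict between 20% and tenfold, where the article states both numbers itself.

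Three stronger readings are tempting and are not supported.

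- **That fivefold and tenfold contradict each other.** They belong to different analyses. The result is different training shares (80% and 90% in plain cross-validation) and different splits, not a contradiction. Each scheme still gives every patient one out-of-fold prediction, so pairing by patient remains possible.
- **That all the planned intervals are too narrow, with coverage near 70%.** That figure belongs to ten repeated 80/20 splits, which the article does not mention and which could concern only the sign models. Under the hold-out reading the interval would be wide.
- **That the fivefold t interval is narrow on average.** In the discriminant simulation its mean half-width was 0.107 (80 v 40) and 0.129 (40 v 40, 8 features), against 0.090 and 0.117 for 1.96 times the true SD. Coverage was still short, because an interval on four degrees of freedom must be wider than that on average to reach 95%.

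Both simulations used simple learners, whereas the plan names convolutional, recurrent and transformer networks. That limits the exact figures. The shortfall appeared with both learners and in every setting tried.

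**Conclusion.** The concern holds in limited form. The 20% test share and the tenfold label cannot both describe a plain cross-validation of 160 patients. The readings that rescue them need something unstated and give intervals that differ more than twofold in width. This is certain from the text, but it affects the ultrasound-sign models rather than the primary outcome.

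For the primary outcome, intervals built from the spread of five folds would under-cover: mildly with a t quantile (about 88–93%) and clearly with 1.96 (about 77–85%). This rests on reading the phrase as fold spread, which is the natural reading but not the only one, and on the assumed learners and feature numbers. The point estimates are not in question. The text should be corrected before any model is evaluated.

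**What to change.** **Partition.** Preferably, fix one patient-level, diagnosis-stratified fivefold partition and use it for the audio models, the ultrasound deep-learning models and the ultrasound-sign models. Each fold would hold 32 patients: 8 IPF, 8 NSIP, 8 COPD and 8 controls. If a 20% hold-out with tenfold tuning in the other 80% was intended, say so explicitly and accept the wider interval shown above.

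**Intervals.** Name the method. Replace fold spread with the overlap-corrected variance s² × (1/J + n_test/n_train) and a t quantile on J − 1 degrees of freedom. A patient-level bootstrap of pooled out-of-fold predictions is a weaker alternative: at 89–90% it did no better than the uncorrected t interval.

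**Cost.** Analysis wording and trivial computing, with no new patients or data. Corrected fivefold intervals are 1.5 times as wide as uncorrected t intervals. For example, the mean half-width of 0.107 at 80 v 40 becomes about 0.16 (0.107 × 1.5). At 97% simulated coverage they err slightly on the wide side.
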